## Abstract

Rationale: high premium is placed on infertility in Nigerian culture. Data is limited on its association with emotional problems in Nigeria. Aims: to develop content for a culturally relevant and cost-effective psychoeducational intervention package and to evaluate its effectiveness for reducing symptoms of anxiety and depression. Sample size estimate: Methods and design: a multi-method study design including development and validation (which includes focus group discussions) of an audio-visual tool which will serve as the intervention in a randomized controlled trial. Data will be analyzed with interim and survival analyses. Population studied: one hundred and 138 (68 per group) infertile women attending infertility clinic in Ibadan. Study outcomes: anxiety and depressions scores assessed with the hospital depression and anxiety scale (HADS) at 0, 3 and 6 weeks. Discussion: it is hoped that the use of the audio-visual tool will improve participants depression and anxiety scores and that the tool will be used for education in routine clinic use and community awareness on psychosocial effects of infertility.

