
### Phase II: randomized controlled trial to test the effectiveness of the psychoeducational intervention

**Study design:** a randomized controlled trial with an allocation ratio of 1: 1 will be utilized.

**Study setting:** 1) University College Hospital (UCH), Ibadan, Nigeria: it serves as a referral tertiary center for Nigeria and sub-Saharan Africa. The study will be at the outpatient gynecology clinic of the hospital; 2) Adeoyo Maternity Hospital (AMH), Yemetu, Ibadan, Nigeria: this is a province-owned secondary health care facility.

**Study subjects:** women attending gynecology clinics in UCH or AMH on account of infertility. Consenting participants will be randomized into the intervention and control arms of the study, respectively.

**Eligibility criteria:** women aged 18 years and above, who have been trying to conceive for at least one year, and who do not have any children.

**Interventions:** consecutive, eligible infertility clinic attendees will be invited to participate in the study and informed consent obtained. Sociodemographic data would be collected via a structured questionnaire. Baseline assessment on participants' psychological and emotional state will be collected via Hospital Anxiety and Depression Scale (HADS) [28]. Thereafter, the participants will be allocated into study groups. Participants in the intervention arm will attend the intervention session on a specified date at the facility. The psychoeducational video will be viewed, and immediate feedback will be obtained. Participants in the control arm will also receive the usual treatment offered all attendees at the gynecology clinics - comprising health talks by public health nurses and explanations and counselling provided by the managing physicians. The study´s primary outcomes are depressive and anxiety symptoms. HADS is a self-assessment scale which has subscales that measure severity of anxiety and depression. It is validated for use in medical outpatient clinics. Participants are followed up at three and six weeks; HADS will be administered at both times. Participants will be counseled on the need for follow-up. Recruited respondents in both arms will receive phone call reminders ahead of scheduled clinic appointments to improve attendance and minimize loss to follow-up.

**Sample size estimation:** the minimum sample size was determined using the formula for comparing two means i.e.

$$\text{n=}\frac{2{\left[Z_{1-\alpha /2}+Z_{1-\beta }\right]}^{2}}{\Delta^{2}}$$

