where Δ, effect size =

$$\Delta =\frac{\mu_{1}-\mu_{1}}{\sigma }$$

where Z1-α/2 [α] was set at 5% i.e. 1.96; Z1-β [β] was set at 20% i.e. power at 80% = 0.84 [29]. A moderate effect size of 0.53 was used. A minimum sample size of 57 was calculated. Attrition rate of 20% was incorporated in the calculation and sample size was estimated at 68 women in each group.

**Randomization procedure:** a randomization list of randomly permuted blocks of treatment assignments in blocks of 4 will be prepared by the study statistician, using a computer-generated table of random numbers. The research assistant will open the sealed envelope containing the assigned group after baseline HADS has been administered. The clinical staff recruiting participants and the data analyst will be blinded, as he will receive two spreadsheets of data without knowing which is the intervention arm.

**Data management and analysis:** the data collected will entered into the computer and analysed using IBM SPSS version 23.0. Interim analysis will be carried out using Mann-Whitney-U test to compare independent samples of the intervention and control groups at 0, 3 and 6 weeks. Survival analysis will also be carried out at each time to assess number of cases of depression or anxiety that transited to non-cases (Figure 1). A data monitoring committee is not necessary as there are no interventions bordering on patient safety. There are no issues that might necessitate termination of trial. Malfeasance or adverse events are not applicable in a trial that constitutes audiovisual expert education as the intervention.

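### The abstract's total of 138 women does not agree with 68 per group at 1:1 allocation, which gives 136

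*Protocol article*

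**What the plan says.** The abstract of the protocol article describes the population as "one hundred and 138 (68 per group) infertile women attending infertility clinic in Ibadan". The total is garbled, part in words and part in digits, and the per-group number stands beside it in brackets.

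The Phase II section sets the structure from which a total should follow. Under study design, "a randomized controlled trial with an allocation ratio of 1: 1 will be utilized". Under study subjects, there are two arms: "Consenting participants will be randomized into the intervention and control arms of the study, respectively". Under sample size estimation, the "sample size was estimated at 68 women in each group".

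The same paragraph gives the inputs. Alpha "was set at 5% i.e. 1.96" and beta "was set at 20% i.e. power at 80% = 0.84". For the effect, "A moderate effect size of 0.53 was used", and from these "A minimum sample size of 57 was calculated". An attrition rate of 20% was then allowed for, which took 57 to 68.

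No other total appears in the text available. Figure 1, the participant flow diagram, is not reproduced there and could not be checked.

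**The concern.** With two equal groups, the total is twice the group size. Twice 68 is not 138, so the abstract contradicts itself within one phrase and also disagrees with the methods. Condensing a longer protocol does not explain this, because the article prints both numbers.

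The planned sample size is a figure that readers, registries and later reports rely on. The number finally randomised will be compared with it, and this is the only total in the text. A reader should not have to guess whether the plan was 136 or 138. What is at stake is the clarity of the stated target, not the validity of the trial.

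**Working it through.** **Inputs** (all from the protocol article)

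- Total: 138 (abstract)
- Per group: 68 (abstract, and Phase II sample size estimation)
- Arms and ratio: two arms, 1:1 (Phase II study design and study subjects)
- z values 1.96 and 0.84, effect size 0.53, minimum 57, attrition 20% (Phase II sample size estimation)

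**Step 1: reproduce the per-group figure.** The article's formula is n = 2(z₁ + z₂)²/Δ².

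2 × (1.96 + 0.84)² / 0.53² = 2 × 7.84 / 0.2809 = 55.8

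This rounds up to 56 per group, against the stated 57. The difference of one woman is immaterial here.

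The 68 follows if 20% is added to 57: 57 × 1.2 = 68.4, printed as 68. It does not follow from dividing by the retained fraction: 57 / 0.8 = 71.25, so 72.

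**Step 2: total from the per-group figure.** 2 × 68 = 136, against 138 printed. The difference is two women. A total of 138 would need 138 / 2 = 69 per group, a figure that the article gives nowhere.

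**Step 3: effect on power.** With 20% attrition, the evaluable number per group is m = 0.8n. By the normal approximation, power = Φ(Δ√(m/2) − 1.96).

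| Per group | Total | Evaluable per group | Δ√(m/2) − 1.96 | Power |
|---|---|---|---|---|
| 68 | 136 | 68 × 0.8 = 54.4 | 0.53 × √27.2 − 1.96 = 0.804 | 78.9% |
| 69 | 138 | 69 × 0.8 = 55.2 | 0.53 × √27.6 − 1.96 = 0.824 | 79.5% |
| 72 | 144 | 72 × 0.8 = 57.6 | 0.53 × √28.8 − 1.96 = 0.884 | 81.2% |

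The choice between 136 and 138 moves power by 79.5 − 78.9 = 0.6 percentage points. Neither total leaves 57 evaluable women per group after 20% attrition.

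**The case against.** The strongest defence is that this is a typing error in an abstract. The phrase is visibly garbled, the methods section is the operative text, and 68 per group is given in both places. The figure of 138 occurs once. On that view the design is not in doubt, and two women change neither validity nor interpretation. Most of this stands. It is the reason to call the error minor. It does not remove the error, because the garbled figure is the only total in the text and costs almost nothing to correct.

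Three stronger readings are tempting, and the article does not support them.

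- **That recruitment or the randomisation list will run to the wrong number.** Nothing says that the hospitals or the statistician work from the abstract's total. The methods give 68 per group without ambiguity.
- **That 138 is faulty because it is not a multiple of the block size of 4 (138 / 4 = 34.5, while 136 / 4 = 34).** This assumes one list across both hospitals, which the article does not say. In any case, an incomplete last block can unbalance the arms by at most two women and causes no bias.
- **That 138 shows an intended 69 per group, from rounding 68.4 up.** The arithmetic fits, but the article does not give this origin, and a slip for 136 fits as well.

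It is also fair to object that simply writing 136 would leave the attrition shortfall unmentioned. That objection stands, and the fix takes it up.

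**Conclusion.** The abstract's total is wrong by the article's own figures: 68 per group in two equal arms is 136, not 138. The finding rests only on the stated per-group number and the 1:1 ratio, and the arithmetic is exact.

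The error is minor: two women and about 0.6 points of power. The power figures assume a two-sided 5% test, an effect size of 0.53, 20% loss in each arm and the normal approximation for comparing two means.

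The more natural correction is 136, because 68 appears in both the abstract and the methods. The article does not prove that 68 rather than 138 was the intended figure, so the sponsor should confirm it. The attrition shortfall is a separate matter from the misprint and does not make the misprint more serious. It matters here because restating 68 per group without comment would repeat a number that does not deliver the 57 evaluable women per group it was meant to secure.

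**What to change.** Replace the total in the abstract with a single number equal to twice the confirmed per-group size, and give the same total in the sample size paragraph. If 68 per group stands, that number is 136.

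If 68 is kept, add a sentence to the sample size paragraph saying that 20% attrition leaves about 54 evaluable women per group (68 × 0.8 = 54.4), not 57, with about 79% power at an effect size of 0.53. If the sponsor instead wants to retain 57 evaluable per group at 20% attrition, the per-group number is 72 and the total 144. The abstract and methods should then both say so.

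Keeping 68 costs only a correction to the abstract and one or two sentences in the methods. Moving to 72 would mean recruiting 144 − 136 = 8 more women than under 68 per group; correcting the misprint does not require it.

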## Study protocol

### Introduction

Infertility is defined as “a disease of the reproductive system defined by the failure to achieve a clinical pregnancy after 12 months or more of regular unprotected sexual intercourse” [1]. From Demographic and Health Surveys (DHS) from developing countries, one in four couples is affected by infertility [2]. High premium is placed on childbirth in Nigeria; all couples are traditionally expected to procreate. Nigeria's DHS does not report infertility prevalence, however, rural community surveys reported prevalence of 8.7% [3] and 30.3% [4]. Infertility constitutes 24-59% of gynecological consultations in Nigeria [5-8].

Infertile women have feelings of loss, grief, anger, sadness, shame, self-blame and lack of femininity [9,10], which predict actual psychopathology [11]. Though a couple's problem, the woman bears the larger burden of the associated stigma, due to socio-cultural beliefs that reproduction is the woman´s primary responsibility, and a failure is her failing [12,13]. Studies show that infertile women are more likely to be economically disadvantaged [14], suffer psychological distress [15], be socially stigmatized [12,14,16] and suffer intimate partner violence [17], than fertile women. The resulting marital disharmony may lead to divorce, for which the woman is blamed [18]. Infertile men may also have more anxiety and depression symptoms than fertile men [19], but these appear to be less than those suffered by their partners [20].

Nigerian studies have suggested counselling and psychological interventions to ameliorate the documented psychosocial aspects of infertility [15,20,21]. However, no interventional studies were found on the subject. Evidence from outside of sub-Saharan Africa suggests that psychosocial interventions for infertile couples are effective [22-24]. An innovative approach to intervention delivery is the use of eHealth programming, “the use of emerging interactive technologies [e.g. internet, CD-ROMs etc.] to enable health improvement and health care services” [25]. These have the advantage of not requiring facilitators and being reproducible and consistent across time and location.

This study proposes to identify psychosocial and emotional needs in infertile women, develop an interventional ehealth tool and determine its effectiveness in improving the psychological and emotional health of infertile women. Traditional one-on-one counselling as part of on-going infertility evaluation and care is often difficult to perform in the study environment, due to lack of skills in gynecologists and stigma attached to seeing a psychiatrist. Integrating mental health care into regular infertility clinics may also be difficult due to dearth of providers.

The authors hope to employ eHealth to combine theoretic knowledge and coping skills with drama, which is a popular form of local entertainment. This is a concept coined as 'edutainment', “entertainment (as by games, films, or shows) that is designed to be educational” [26]. If effective, this intervention does not require face-to-face counselling. Family and close friends can also watch and can be educated on supporting the infertile couple. The aims of the study are to: 1) develop content for a culturally-relevant and cost-effective psychoeducational intervention package aimed at reducing social and emotional problems among women with infertility in Ibadan, Nigeria; 2) translate the developed content into an audio-visual drama production as a user-friendly tool for the target audience; and 3) evaluate the effectiveness of this psychoeducational intervention for reducing symptoms of anxiety and depression among women with infertility in Ibadan, Nigeria.

### Methods

A multi-method study design will be utilized and implemented in two phases; phase i: development and validation of audio-visual psychoeducational intervention material; phase ii: exploratory randomized controlled trial to test the effectiveness of the intervention. The development of psychoeducational material will be a multi-disciplinary process involving the following specialists - psychiatrist, gynecologist, public health physician and communication and language arts expert. Theatre arts' professionals and students will also be recruited subsequently. The two phases are described below.

**Phase I: development of psychoeducational intervention material:** this will be conducted in the following steps: 1) Content development: a) literature review: a comprehensive review of the literature will be performed and a composite list of emergent themes that affect women with infertility globally and especially in the Nigerian socio-cultural setting, will be developed. This will be independently performed by two units of two members each, with subsequent harmonization of both lists by the research group through discussions and consensus; b) gender consideration: two focus group discussions (FGDs) and several key informant interviews (KIIs) of infertile males (or spouses of infertile women) will be organized to understand the perceptions and experiences of males with respect to issues of infertility. This is important, as only few studies conducted among men were found in literature [20,27], resulting in little being known about male experience. The investigators hope to gain a holistic understanding from both male and female perspectives, which should strengthen the content development process of the psycho-educational intervention; c) specialist input from gynecologists and psychiatrists: the gynecologists will provide a summary sheet about the causes, course, treatment options and outcomes of infertility globally and in the study environment. The psychiatrists will also provide summary points about coping skills and building resilience in the face of life challenges as an essential life skill; d) emergence of the psychoeducational content: the combination of information derived from the three sources above will then be distilled by two units working independently to develop the psychoeducational content. Both teams will then meet to harmonize and resolve areas of disagreement and to produce a final summative material that is arranged into themes. 2) Translation of the developed content into a storyline and script. The content as developed in step 1 will be transformed into a storyline with specific emphasis on effective communication and message impact for the target audience. This will be overseen by the communications and language arts expert. 3) Production of psychoeducational intervention video: the script will be acted by professional actors, as well as students of the Department of Theatre Arts of the University of Ibadan, to produce a short film which will illustrate and deliver the key messages derived from the content. 4) Pre-test and establishment of face validity: the final video produced to deliver the psychoeducational intervention will be pretested and screened to a selection of nurses and doctors (independent of the study team) and 6-10 women with infertility (drawn from a different facility, other than the proposed study sites). Their feedback and views will be sought thereafter for acceptability, critical feedback and comments. The production will be edited as appropriate, following this screening.

### Phase II: randomized controlled trial to test the effectiveness of the psychoeducational intervention

**Study design:** a randomized controlled trial with an allocation ratio of 1: 1 will be utilized.

**Study setting:** 1) University College Hospital (UCH), Ibadan, Nigeria: it serves as a referral tertiary center for Nigeria and sub-Saharan Africa. The study will be at the outpatient gynecology clinic of the hospital; 2) Adeoyo Maternity Hospital (AMH), Yemetu, Ibadan, Nigeria: this is a province-owned secondary health care facility.

**Study subjects:** women attending gynecology clinics in UCH or AMH on account of infertility. Consenting participants will be randomized into the intervention and control arms of the study, respectively.

**Eligibility criteria:** women aged 18 years and above, who have been trying to conceive for at least one year, and who do not have any children.

**Interventions:** consecutive, eligible infertility clinic attendees will be invited to participate in the study and informed consent obtained. Sociodemographic data would be collected via a structured questionnaire. Baseline assessment on participants' psychological and emotional state will be collected via Hospital Anxiety and Depression Scale (HADS) [28]. Thereafter, the participants will be allocated into study groups. Participants in the intervention arm will attend the intervention session on a specified date at the facility. The psychoeducational video will be viewed, and immediate feedback will be obtained. Participants in the control arm will also receive the usual treatment offered all attendees at the gynecology clinics - comprising health talks by public health nurses and explanations and counselling provided by the managing physicians. The study´s primary outcomes are depressive and anxiety symptoms. HADS is a self-assessment scale which has subscales that measure severity of anxiety and depression. It is validated for use in medical outpatient clinics. Participants are followed up at three and six weeks; HADS will be administered at both times. Participants will be counseled on the need for follow-up. Recruited respondents in both arms will receive phone call reminders ahead of scheduled clinic appointments to improve attendance and minimize loss to follow-up.

**Sample size estimation:** the minimum sample size was determined using the formula for comparing two means i.e.

$$\text{n=}\frac{2{\left[Z_{1-\alpha /2}+Z_{1-\beta }\right]}^{2}}{\Delta^{2}}$$

where Δ, effect size =

$$\Delta =\frac{\mu_{1}-\mu_{1}}{\sigma }$$

where Z1-α/2 [α] was set at 5% i.e. 1.96; Z1-β [β] was set at 20% i.e. power at 80% = 0.84 [29]. A moderate effect size of 0.53 was used. A minimum sample size of 57 was calculated. Attrition rate of 20% was incorporated in the calculation and sample size was estimated at 68 women in each group.

**Randomization procedure:** a randomization list of randomly permuted blocks of treatment assignments in blocks of 4 will be prepared by the study statistician, using a computer-generated table of random numbers. The research assistant will open the sealed envelope containing the assigned group after baseline HADS has been administered. The clinical staff recruiting participants and the data analyst will be blinded, as he will receive two spreadsheets of data without knowing which is the intervention arm.

**Data management and analysis:** the data collected will entered into the computer and analysed using IBM SPSS version 23.0. Interim analysis will be carried out using Mann-Whitney-U test to compare independent samples of the intervention and control groups at 0, 3 and 6 weeks. Survival analysis will also be carried out at each time to assess number of cases of depression or anxiety that transited to non-cases (Figure 1). A data monitoring committee is not necessary as there are no interventions bordering on patient safety. There are no issues that might necessitate termination of trial. Malfeasance or adverse events are not applicable in a trial that constitutes audiovisual expert education as the intervention.

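### The case-to-non-case analysis rests on baseline HADS cases only, yet allocation ignores the baseline HADS, so the number and split of cases are left to chance and the stated 80% power does not cover that analysis

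*Protocol article*

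**What the plan says.** All references are to the protocol article, Phase II unless stated.

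- Eligibility criteria: entry is open to "women aged 18 years and above, who have been trying to conceive for at least one year, and who do not have any children". Under Interventions, "consecutive, eligible infertility clinic attendees will be invited to participate in the study and informed consent obtained". Neither sets a symptom level.
- Introduction, aim 3: to "evaluate the effectiveness of this psychoeducational intervention for reducing symptoms of anxiety and depression among women with infertility in Ibadan, Nigeria".
- Sample size estimation: "A moderate effect size of 0.53 was used", giving 57 per group, raised to 68 for 20% attrition. The population to which 0.53 refers is not named.
- Randomization procedure: one list in permuted blocks of 4 is described, with no stratification factor. "The research assistant will open the sealed envelope containing the assigned group after baseline HADS has been administered".
- Data management and analysis: Mann-Whitney comparisons of the arms at 0, 3 and 6 weeks, plus a survival analysis to "assess number of cases of depression or anxiety that transited to non-cases".
- Table 3: cases and non-cases compared between arms by chi-square at baseline, 3 and 6 weeks, so women who are not cases at baseline are expected in the sample.

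**The concern.** Two analyses run on two different sets of women. The score comparison and the Table 3 chi-square use everyone. The transition analysis can use only women who start as cases, because a woman who is not a case cannot leave that state. The plan sizes the first set and says nothing about the size of the second.

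The plan also collects, before allocation, the one measurement that would control the second set, and then does not use it. The baseline value of the outcome scale is normally the strongest prognostic factor for the later value. If more cases fall in one arm by chance, the Mann-Whitney and chi-square comparisons at 3 and 6 weeks, neither of which is described as adjusting for baseline, start from an uneven position. A reader might also take the 80% power as covering the transition result, which it does not.

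**Working it through.** **Inputs.** From the article: effect 0.53, two-sided 5% (1.96), 80% power (0.84), 57 per group before attrition, 68 randomised per group, 1:1 allocation. Assumed, because the article does not give it: a share p of baseline cases, shown at 30%, 50% and 70%.

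**1. The plan's own figure.** n = 2(1.96 + 0.84)² / 0.53² = 15.68 / 0.2809 = 55.8, so 56 per group. A t-test calculation gives 56.9. The stated 57 is reproduced for a comparison of means in all randomised women. Then 57 × 1.2 = 68.4, which gives the stated 68.

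**2. Women who can enter the transition analysis.** Cases per arm = p × 57 evaluable (p × 68 randomised):

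- 30%: 17 (20)
- 50%: 29 (34)
- 70%: 40 (48)

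**3. Chance difference in cases between arms.** Without stratification, blocks of 4 balance the arm totals but not the cases. The SD of the difference in case counts is √(2 × 68 × p(1 − p)).

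- p = 50%: √34 = 5.83; 1.96 × 5.83 = 11.4, about ±11 women, or 11/68 = 16 percentage points in baseline case share.
- p = 30% or 70%: √28.56 = 5.34; 1.96 × 5.34 = 10.5, about ±10 women.

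**4. What that difference does.** Within the transition analysis, an uneven split costs little precision. With 68 cases divided 40 to 28, the equivalent equal size is 2 × 40 × 28 / 68 = 32.9 per arm, against 34. The larger effect is on the comparisons in all women at 3 and 6 weeks, where a 16-point gap in case share at baseline carries forward to the extent that caseness persists.

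**5. What the transition analysis could detect.** As an illustration, assume 30% of control cases become non-cases. With 29 cases per arm, 80% power needs about 66% in the intervention arm. With 57 cases per arm it would need about 56%. The detectable difference is thus about 36 percentage points instead of 26.

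**6. After stratification.** In a stratum list of complete blocks of 4, the arms are equal. An unfinished last block can leave them at most 2 apart. The chance range of ±11 becomes at most 2 per list.

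**The case against.** The strongest reply is that unselected entry is the question being asked. Aim 3 concerns women with infertility, not HADS cases. Attendees are recruited consecutively, the abstract foresees routine clinic and community use, Table 3 has a non-case row at baseline, and the trial is called exploratory. All of this stands, and the entry criteria are not at fault.

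A reader might go further and infer that women without caseness dilute the planned effect, so that the trial is badly underpowered and entry should be limited to cases. If 0.53 held in cases only, the rest gained nothing and the SD were unchanged, the overall effect would be p × 0.53 = 0.16, 0.27 or 0.37, and t-test power at 57 per arm would be about 13%, 29% or 50% at 30%, 50% or 70% cases. The document does not support that reading. It does not say that 0.53 describes cases. The formula is applied to the population enrolled, and if 0.53 is the average effect there, any dilution is already in it. Women below a case cut-off can still improve on the score: if they gained half the effect seen in cases, the same powers would be about 45%, 56% and 66%, still on the premise that 0.53 belongs to cases alone. Case-only entry would also change the question. Entry on either subscale would still admit women who are not cases on the other.

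Two further replies carry some weight. Women who are not cases at baseline do contribute to Table 3, since they may become cases. And a condensed article may leave a stratification factor to the full protocol, so the point is made on the procedure as described. Neither reply changes who can enter the transition analysis.

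**Conclusion.** The point holds in a limited form. Open entry is consistent with the aim. What is fixed badly is that an analysis restricted in effect to baseline cases is planned without control of how many cases each arm receives, although the measurement needed is taken before allocation. At an assumed 50% case share, the chance difference is about ±11 women between arms of 68, and about 29 of 57 evaluable women per arm inform the transition analysis (17 to 40 over 30% to 70%).

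The case share is an assumption, as is the 30% control transition rate in the illustration. The direction depends on neither: at any share below 100%, fewer than 57 women per arm are available and the 80% power does not carry over. That baseline HADS is strongly prognostic is general statistical experience; the article gives no correlation. The consequence is moderate, an avoidable chance imbalance and an unstated limit on one analysis, not a failed sample size for the score comparison.

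**What to change.** 1. Keep the entry criteria. Restricting entry to HADS cases is a trade-off for the investigators and is not needed here.
2. Score the baseline HADS before the envelope is opened, and stratify the blocks of 4 by baseline case status (case on either subscale: yes or no). Use the cut-off that Tables 2 and 3 will use, and write it into the protocol. The stratum should also be carried into the analysis.
3. State in Sample size estimation that 0.53 and 57 per group refer to the score comparison in all attendees, and that the 80% power does not apply to the transition analysis in baseline cases. Stratification evens out the split but does not add cases.

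Cost: immediate scoring of a form already completed, and two envelope sets instead of one. A single either-subscale factor balances anxiety cases and depression cases only in part when each is counted separately. That is a reasonable price for keeping to two strata with 68 women per arm.
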